# Diagnostic Ability of a Smartphone App for Dry Eye Disease: Protocol for a Multicenter, Open-Label, Prospective, and Cross-sectional Study

**DOI:** 10.2196/45218

**Published:** 2023-03-13

**Keywords:** digital health, digital therapeutics, dry eye disease, Japanese version of the Ocular Surface Disease Index, maximum blink interval, mobile health, smartphone, smartphone app, tear film breakup time, telemedicine

## Abstract

**Background:**

Dry eye disease (DED) is one of the most common ocular surface diseases. Numerous patients with DED remain undiagnosed and inadequately treated, experiencing various subjective symptoms and a decrease in quality of life and work productivity. A mobile health smartphone app, namely, the DEA01, has been developed as a noninvasive, noncontact, and remote screening device, in the context of an ongoing paradigm shift in the health care system, to facilitate a diagnosis of DED.

**Objective:**

This study aimed to evaluate the capabilities of the DEA01 smartphone app to facilitate a DED diagnosis.

**Methods:**

In this multicenter, open-label, prospective, and cross-sectional study, the *test method* will involve using the DEA01 smartphone app to collect and evaluate DED symptoms, based on the Japanese version of the Ocular Surface Disease Index (J-OSDI), and to measure the maximum blink interval (MBI). The *standard method* will then involve a paper-based J-OSDI evaluation of subjective symptoms of DED and tear film breakup time (TFBUT) measurement in an in-person encounter. We will allocate 220 patients to DED and non-DED groups, based on the *standard method*. The primary outcome will be the sensitivity and specificity of the DED diagnosis according to the *test method*. Secondary outcomes will be the validity and reliability of the *test method*. The concordance rate, positive and negative predictive values, and the likelihood ratio between the *test* and *standard methods* will be assessed. The area under the curve of the *test method* will be evaluated using a receiver operating characteristic curve. The internal consistency of the app-based J-OSDI and the correlation between the app-based J-OSDI and paper-based J-OSDI will be assessed. A DED diagnosis cutoff value for the app-based MBI will be determined using a receiver operating characteristic curve. The app-based MBI will be assessed to determine a correlation between a slit lamp–based MBI and TFBUT. Adverse events and DEA01 failure data will be collected. Operability and usability will be assessed using a 5-point Likert scale questionnaire.

**Results:**

Patient enrollment will start in February 2023 and end in July 2023. The findings will be analyzed in August 2023, and the results will be reported from March 2024 onward.

**Conclusions:**

This study may have implications in identifying a noninvasive, noncontact route to facilitate a diagnosis of DED. The DEA01 may enable a comprehensive diagnostic evaluation within a telemedicine setting and facilitate early intervention for undiagnosed patients with DED confronting health care access barriers.

**Trial Registration:**

Japan Registry of Clinical Trials jRCTs032220524; https://jrct.niph.go.jp/latest-detail/jRCTs032220524

**International Registered Report Identifier (IRRID):**

PRR1-10.2196/45218

## Introduction

Dry eye disease (DED) is one of the most frequently encountered ocular surface diseases, with a prevalence ranging from 5% to 50% [1,2], which is projected to increase, likely due to the worldwide trend toward an aging population and lifestyle changes associated with a digitalized society [1-4]. DED-related symptoms are detrimental to quality of life (QoL) and work productivity, leading to society-wide economic loss [5,6]. Subjective DED-related symptoms are highly variable and include ocular dryness, eye discomfort, eye strain, decreased visual acuity, and photophobia [7-11]. Additionally, DED is highly heterogeneous, with patients presenting with seemingly unpredictable combinations of the abovementioned symptoms. Therefore, patients with DED are prone to having their nonspecific presentations overlooked, and many are left undiagnosed without appropriate management [3,9,12-14]. There is no definitive cure for DED, and current standards of care comprise ex post facto symptom management, highlighting the importance of early diagnosis and intervention to prevent disease progression and longstanding damage [15-19].

Concerning DED diagnosis, Tear Film & Ocular Surface Society and Asian Dry Eye Society criteria recommend evaluating a patient’s subjective symptoms and tear film breakup time (TFBUT) [20,21]. However, TFBUT measurement is inherently invasive owing to the need for sodium fluorescein application, and measurements under light microscopy are required [20-23]. The ongoing COVID-19 pandemic has also increased the demand for a noninvasive alternative that could be used in remote settings [24,25]. One major obstacle to DED diagnosis in the context of telemedicine is the inability to evaluate the ocular surface and the use of slit-lamp microscopy in TFBUT, and clinicians may be solely reliant on subjective symptoms for diagnosis. Therefore, identification of a novel proxy for existing invasive examinations is needed for a reliable, noninvasive DED diagnosis.

Recent studies have suggested the maximum blink interval (MBI) measurement as a noninvasive alternative to TFBUT, with the MBI defined as the maximum length of time a patient is able to keep their eyes open between 2 blinks [26]. A positive correlation has been reported between the MBI and TFBUT, likely owing to the MBI’s capability to reflect ocular surface integrity [26-30]. The simplicity and noninvasive nature of MBI measurements underscores its candidacy as an alternative to TFBUT for screening purposes. Our earlier studies have indicated that the concomitant use of the MBI and the Ocular Surface Disease Index (OSDI) questionnaire can determine DED with similar accuracy to standard diagnostic methods using TFBUT and the OSDI [31,32].

Mobile health (mHealth) is defined by the World Health Organization as “medical and public health practice supported by mobile devices, such as mobile phones, patient monitoring devices, personal digital assistants (PDAs), and other wireless devices” [33]. The capability of mHealth to digitally perform therapeutic activities has raised the interest of clinicians and providers due to its potential use in disease prevention, diagnosis, and treatment through commonplace smart devices [32,34-39]. Previous studies concerning the validity and reliability of smartphone-based administration of MBI examinations and OSDI questionnaires yielded a satisfactory result [3,32,40]. Reported findings suggest that noninvasive and nonintrusive DED screening during activities of daily living may be possible, enabling an earlier DED diagnosis and interventions in remote settings [40,41]. More importantly, this possibility may have implications in accurately identifying undiagnosed patients with DED, allowing for timely intervention, preventing a further decrease in QoL, and reducing societal economic loss.

In this clinical study, we intend to use an in-house smartphone app, namely, the DEA01, which has been designed as an investigational device to facilitate a DED diagnosis. This study will aim to evaluate the capabilities of the DEA01 in facilitating a diagnosis of DED.

## Methods

### The DEA01 Smartphone App

The DEA01 smartphone app for DED diagnostic assistance was developed by InnoJin, Inc. It will be available on Apple’s App Store and the Google Play Store. As of December 2022, it has not yet been approved as software for a medical device in Japan.

The DEA01 collects dry eye symptoms using the OSDI and MBI to facilitate a DED diagnosis [32]. Blinking is measured using the smartphone camera and the *CIFaceFeature* function in the iOS interface for facial detection. DEA01 version 1.0 will be installed on an iPhone 13 Pro (Apple Inc). The app will be modified should minor issues arise during the study. Screenshots of the current version of the DEA01 (December 2022) are shown Figure 1.

**Figure 1 figure1:**
[figure not shown]
Screenshots of DEA01: screenshots of the (A) welcome screen, (B) Ocular Surface Disease Index (OSDI) questionnaire, (C) measurement of the maximum blink interval, and (D) examination result screen for dry eye diagnostic assistance.

### Objective

This study’s primary objective is to evaluate DED diagnostic accuracy using the DEA01 smartphone app compared with standard DED diagnostic methods.

### Study Design

In this multicenter, open-label, prospective, and cross-sectional study, patients will be evaluated for DED using the DEA01 (*test method*). A physician will then provide a DED diagnosis based on 2016 Asia Dry Eye Society criteria [20] (*standard method*). To ensure that the *test method* will not affect a patient’s treatment plan, the physician will make a diagnosis using only *standard method* results without reviewing *test method* results. A minimum number of 220 patients will be enrolled, with patients allocated into a DED group or a non-DED group based on the diagnosis obtained using the *standard method*. The study design is shown in Figure 2.

**Figure 2 figure2:**
[figure not shown]
Study flowchart. DED: dry eye disease.

### Ethics Approval

This study has been approved by the Juntendo University Certified Review Board, Tokyo, Japan (approved protocol V.1.1.1, dated December 19, 2022; approval number: J22-003). Patients will have the option to voluntarily provide written informed consent to participate in the study. Written consent will be obtained from a patient’s parent or legal guardian for patients aged <20 years. All involved parties will make every effort to protect study patients’ personal information and privacy. Patient-related data will be anonymized, and research-related data and the smartphones used in this study will be stored in locked lockers at each collaborating institution, with access strictly controlled by the research staff. All patients will receive a 1000-yen (US $7.77) voucher.

### Study Setting

This study will be conducted between February 1, 2023, and November 30, 2023. Patients will be recruited from the Departments of Ophthalmology at 3 medical institutions, namely, Juntendo University Hospital, Tokyo, Japan [42]; Toho University Omori Medical Center, Tokyo, Japan; and Tokyo Dental College Ichikawa General Hospital, Chiba, Japan.

### Patient Selection

Outpatients who visit the Ophthalmology Departments of the cooperating hospitals will be recruited for the study. Enrolled patients will include those with DED and other concomitant ocular diseases. Inclusion and exclusion criteria are shown in Textbox 1.

Inclusion and exclusion criteria.
**Inclusion criteria**
Patients with dry eye disease (DED) or suspected DEDPatients aged ≥16 years at the time of providing informed consentPatients able to use smartphonesPatients/guardians who, after receiving a full explanation concerning participation in the study and with a full understanding of the study, voluntarily provide written consent to participate
**Exclusion criteria**
Patients with eyelid closure disorder, ptosis, psychiatric disorders, and Parkinson diseasePatients who wear contact lensesPatients who are unable to comply with the study protocol for physical or mental reasonsPatients whom the principal investigator deems unsuitable to participate in this study

### Patient Withdrawal

Patients will be withdrawn from the study if, due to the occurrence of other diseases, it is deemed difficult to continue the research; if patients or their parents/guardians request to terminate their participation in the research; if the research study is discontinued; or if the principal investigator and subinvestigators determine that it is appropriate to discontinue the research.

### Study Procedures

After enrollment in the study, patients will be evaluated for DED by clinical research coordinators using the DEA01. A physician will diagnose DED using the *standard method* without checking *test method* results. Details regarding the *test method* and *standard method* are shown in Textbox 2.

*Test* and *standard method.*
**
*Test method*
**
Dry eye disease (DED) diagnosis based on the app-based Japanese version of the Ocular Surface Disease Index (J-OSDI) and maximum blink interval (MBI), using the DEA01Patients will respond to the app-based J-OSDI questionnaire and be measured using the app-based MBI on the DEA01. The J-OSDI questionnaire is used to evaluate the subjective symptoms of DED on a 100-point scale [43,44]. The MBI will be defined as the length of time that a patient can keep their eyes open before blinking [26]. The app-based MBI will be measured using the smartphone’s camera on the DEA01 and a visually confirmed MBI will be measured using a stopwatch.
**
*Standard method*
**
DED diagnosis using a paper-based J-OSDI and tear film breakup time (TFBUT)Patients will respond to the paper-based J-OSDI questionnaire and be measured using TFBUT [20]. The diagnosis of DED using the *standard method* will be based on 2016 Asian Dry Eye Society criteria, with positive subjective symptoms (J-OSDI total score ≥13) and decreased TFBUT (≤5.0 s) being used to diagnose DED [20]. Based on the diagnosis using the *standard method*, patients will be allocated to DED and non-DED groups.

### Data Collection and Outcome Assessments

The data collection items are shown in Textbox 3. The assessments will be done according to a predetermined sequence. First, the assessment of subjective symptoms of DED using the app-based J-OSDI and MBI on the DEA01 will be conducted as the *test method* by trained clinical research coordinators. The physician will not be informed of the *test method* results. The physician will then perform clinical examinations for DED, using the *standard method* and ophthalmic examinations. Clinical examinations for DED will include an evaluation of subjective symptoms of DED using the paper-based J-OSDI questionnaire, slit lamp–based MBI, TFBUT, corneal fluorescein staining (CFS), and tear secretion volume using Schirmer test I. The ophthalmic examinations will include measurement of visual acuity, intraocular pressure, and slit-lamp microscopic photography. All examinations will be performed within one day.

Data collection.
**Patients’ characteristics**
Age, sex, medical history, and medication
**
*Test method*
**
Subjective symptoms of dry eye disease (DED) evaluated using the app-based the Japanese version of the Ocular Surface Disease Index (J-OSDI) on the DEA01Visually confirmed maximum blink interval (MBI)App-based MBI
**
*Standard method*
**
Subjective symptoms of DED evaluated using the paper-based J-OSDITear film breakup time
**Other DED examinations**
Corneal fluorescein stainingSlit lamp–based MBITear secretion volume using Schirmer test I
**Ophthalmic examinations**
Visual acuityIntraocular pressureSlit-lamp microscopy
**Other outcomes**
DEA01 failureDEA01 operability and usabilityAdverse events

#### The Japanese Version of the OSDI

The Japanese version of the OSDI (J-OSDI) is a questionnaire comprising 12 questions to evaluate subjective symptoms of DED and has been validated in Japan as an OSDI-equivalent questionnaire for DED diagnosis [43-45]. Patients will answer each question on a scale ranging from 0 to 4, with 0 indicating “none of the time” and 4 indicating “all of the time.” For questions 6 through 12, if a question is not applicable to a patient, they can select “not applicable.” The J-OSDI results are reported on a 100-point scale to determine the severity of DED symptoms. The J-OSDI total score is calculated according to the following formula [43,44]:

**(1)**

#### TFBUT

TFBUT will be measured using sodium fluorescein to assess tear film stability [20]. To minimize the effect of a test strip on tear volume and TFBUT, a small amount of dye will be administered using wet fluorescein strips. After the dye is instilled, the patients will be instructed to blink 3 times to ensure that the dye is uniformly incorporated into the tear film. The time interval between the last blink and the appearance of the first dark spot on the cornea will be measured, and the average value from 3 measurements will be used as the test outcome. A cutoff TFBUT value of ≤5.0 seconds will be used to diagnose DED [20].

#### MBI

The MBI is defined as the length of time that a patient is able to keep their eyes open before blinking during each trial [26]. In the *test method*, the app-based MBI will be measured using the smartphone’s camera on the DEA01, and visually confirmed MBI will be measured using a stopwatch by a trained clinical research coordinator. In the *standard method*, the MBI will be measured by a physician using a slit-lamp microscope. In both methods, the MBI will be measured twice for each patient and the average value will be adopted as the result. An MBI exceeding 30 seconds will be recorded as 30 seconds. The MBI cutoff value will be calculated using receiver operating characteristic (ROC) curve analysis [31].

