**(2)**

Therefore, the minimum sample size will be 100 patients in each group. To meet the minimum required number of patients in each group, the target total number of patients will be set at 110 for each group, assuming a 10% exclusion rate due to missing data.

For the primary end points, the sensitivity and specificity of DED diagnosis using the DEA01 will be calculated using ROC curve analysis with the cutoff value for the app-based MBI in the *test method*. This cutoff value will be calculated using ROC curve analysis [31]. The ROC curve will show sensitivity (positive rate) on the vertical axis and 1-specificity (false positive rate) on the horizontal axis, and the plots will be connected using straight lines. The point at which the sensitivity and specificity for DED diagnosis using the app-based MBI will be maximized and will be set as the cutoff value for MBI [31].

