The secondary outcomes of the overall concordance rate, positive/negative predictive value, and positive/negative likelihood ratio will be calculated by comparing the DED diagnosis results from the *test method* with the results from *standard method* in a mixed matrix. The diagnostic performance of DEA01 will be evaluated through calculating the area under the ROC curve plotted from the sensitivity and specificity of the *test method*. The substitutability of MBI measurement for TFBUT measurement in DED diagnosis will be assessed using ROC curve analysis and through calculating the area under the ROC curve, using the cutoff value of the app-based MBI for TFBUT ≤5 seconds. The internal consistency of the app-based J-OSDI will be evaluated using factor analysis and Cronbach α coefficient, with α>0.70 considered an acceptable range [53]. Correlation and consistency will be evaluated using Pearson or Spearman correlation coefficients, an intraclass correlation coefficient, and Bland-Altman analysis. In each patient group, study patients’ backgrounds will be analyzed using a 2-tailed unpaired *t* test for continuous variables and a chi-square test for categorical variables. If a continuous variable does not clearly follow a normal distribution, it will be appropriately transformed to a logarithm and aggregated with the mean and SD or the median and IQR will be used as descriptive statistics. The operability and usability of the DEA01 will be evaluated in each group using the average score of the 5-point Likert scale responses to the operability and usability questions and the number of patients who answered better or worse than neutral using 2-tailed unpaired *t* and chi-square tests. For safety assessment, the frequency and rate of adverse events will be calculated for each group, and between-group comparisons will be performed using Fisher exact probability or chi-square tests.

A 2-sided level of significance will be set at 5%, and the confidence coefficient will be set at 95%, unless otherwise specified. Missing value completion will not be performed.

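### MBI readings above 30 s are stored as 30 s with no stated treatment in the app-versus-slit-lamp agreement analysis, which pulls the mean difference toward zero and distorts the limits of agreement

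*Protocol article*

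**What the plan says.** Three places in the protocol article combine.

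- **Methods, MBI.** The measure is defined as the "length of time that a patient is able to keep their eyes open before blinking during each trial". The summary rule is "In both methods, the MBI will be measured twice for each patient and the average value will be adopted as the result". The cap is "An MBI exceeding 30 seconds will be recorded as 30 seconds".
- **Secondary Outcomes, item 10.** App-based and slit lamp–based MBI are to be compared for correlation, agreement and difference. The text after the list says that items 10 to 12 serve to establish the validity of the two MBI measurements.
- **Sample Size and Statistical Analyses.** "Correlation and consistency will be evaluated using Pearson or Spearman correlation coefficients, an intraclass correlation coefficient, and Bland-Altman analysis". On incomplete data the only statement is "Missing value completion will not be performed".

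The article does not say whether the cap applies to the single attempt or to the average. The definition by trial favours the attempt. Nor does it say how capped readings are handled in the agreement analyses.

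**The concern.** A stored value of 30 s means at least 30 s. Bland-Altman analysis, the intraclass correlation and Pearson's coefficient all take it as a measured time.

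If both methods are at the cap, the recorded difference is 0. If only one is, the difference is cut short. If one attempt is capped and the other is not, the average is a number that cannot be recognised as affected: 30 s and 14 s give 22 s, the same as an uncapped 22 s.

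Outcome 10 is the evidence that the camera times the interval as the physician does at the slit lamp. A blink missed by the camera lengthens the app reading, so that error runs toward the cap. Capped attempts may not be rare: the plan aims for 110 non-DED patients out of 220, and the Introduction reports a positive correlation between MBI and TFBUT, so long intervals should gather in that half. At stake is whether the reported bias and limits describe agreement over the whole range of MBI or only up to 30 s.

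**Working it through.** **The plan's own figure.** The only computed figure is the sample size: "the minimum sample size will be 100 patients in each group". The formula is not legible in the text at hand. With the usual precision formula, and p = 0.5 assumed, n = 1.96² × 0.5 × 0.5 / 0.10² = 96.04, so 97, which agrees with 100 after rounding up. It concerns sensitivity and specificity and does not depend on the cap.

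**What follows without any distribution.** For any two readings a and b, |min(a, 30) − min(b, 30)| ≤ |a − b|. If both exceed 30 s, the left side is 0. If a = 30 (capped) and b = 12, the recorded difference is still 18 s. So the loss is complete only when both readings reach the cap, partial when one does, and nil when neither does.

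**Effect on classification.** With a per-attempt cap, a patient with one capped attempt averages (30 + x)/2 > 15 s, where x > 0 is the other attempt; the uncapped average is also above 15 s. With a cap on the mean, only averages above 30 s change. Either way, no patient changes side of a cutoff below 15 s.

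**Size, by simulation.** Inputs from the article: cap 30 s, two attempts per method, averaged. Assumed, because the article gives no MBI distribution: log-normal true MBI with log-SD 0.6 and the medians shown; 400,000 patients per scenario; each attempt capped, then averaged. Proportional error means an attempt-level log-SD of 0.3; this reproduces the uncapped bias, since 0.2 × 8 × exp(0.6²/2 + 0.3²/2) = 2.00 s at median 8 s. Constant error has the SD shown, in seconds. Width is 3.92 × SD of the differences.

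| Error model and app over-read | Median MBI | App attempts capped | Bias, uncapped → capped (s) | Limits width, uncapped → capped (s) |
|---|---|---|---|---|
| Proportional, 20% | 8 s | 4.5% | 2.00 → 1.76 | 16.7 → 13.2 |
| Proportional, 20% | 16 s | 25% | 4.02 → 2.21 | 33.5 → 16.4 |
| Proportional, 20% | 20 s | 37% | 5.01 → 2.10 | 41.7 → 16.4 |
| Constant SD 4, 3 s | 8 s | 2.6% | 2.90 → 2.83 | 15.2 → 15.0 |
| Constant SD 4, 3 s | 16 s | 20% | 2.98 → 2.44 | 15.6 → 14.4 |
| Constant SD 1, 3 s | 16 s | 19% | 3.00 → 2.49 | 3.9 → 5.5 |

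The bias moved toward zero in every over-reading scenario. The smallest shift was (2.90 − 2.83)/2.90 = 2%, the largest (5.01 − 2.10)/5.01 = 58%. Capping the mean instead of the attempt leaves the direction the same.

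Ratio of limits width, capped to uncapped, over all scenarios run:

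- 0.39 to 0.84 with proportional error;
- 0.84 to 0.99 with constant SD 4 s;
- 0.86 to 0.97 with constant SD 0.5 to 2 s and no over-read;
- 1.02 to 4.46 with constant SD 0.5 to 2 s and an over-read of 3 to 5 s.

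The last group widens because capped zeros are mixed with uncapped offsets, which adds spread that was not there.

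**The case against.** The strongest reply has five parts.

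1. **The 30 s ceiling may be part of the measure.** Agreement on a 30 s-limited MBI, the quantity the diagnostic rule uses, is a legitimate target. This stands, but it is a narrower claim, and the article does not state it as the target.
2. **Flagging and sensitivity analyses usually belong in the statistical analysis plan, which is not shown.** This stands for the choice of model. It does not cover the recording rule, which the article fixes: if only capped averages are kept, no later plan can tell which are affected.
3. **Other checks exist.** A coordinator times a visually confirmed MBI by stopwatch during the app test, and app failures are recorded. Missed blinks below the cap can be seen there. This reduces the weight of the point but does not help where both readings exceed 30 s.
4. **The size has no basis in the documents.** Correct. With 2.6% of app attempts capped and constant error SD 4 s, the effect is trivial.
5. **Spearman correlation is already permitted**, so requiring it is a preference. Correct.

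A reader might infer more: that app over-reading is hidden, and that the limits of agreement are necessarily too narrow. The documents support neither. Over-reading below the cap stays visible, and it is lost entirely only when both methods reach 30 s. Narrowing depends on an error model that the article does not give; a systematic offset with small random error widens the limits. That last case may be the less likely one here, since the two methods time separate eye-opening attempts and so include the patient's own variation, but it cannot be ruled out.

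**Conclusion.** The point holds in limited form. If the stated rule is followed, the estimated app-versus-slit-lamp mean difference is biased toward zero whenever the app over-reads and some attempts reach 30 s, and the limits of agreement are distorted in a direction that depends on the error structure. The 2% to 58% range rests on assumed log-normal MBI with median 8 to 20 s and on the assumed error models; the share of capped attempts decides where in that range the trial falls, and the article does not give it. That capped values are used as exact times is inferred from the methods named, not stated.

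The scope is secondary outcome 10, with minor relevance to items 11 and 12. The sample size is untouched, and so is diagnostic classification for an MBI cutoff below 15 s. The change is worth making because it costs little and part of the loss is irreversible once data are stored only as averages.

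**What to change.** - Keep both attempts for each method and flag every attempt that reaches 30 s.
- State whether the cap applies to the attempt or to the mean.
- Report the share of capped attempts by method.
- Keep the planned Bland-Altman analysis, described as agreement on the 30 s-limited scale.
- Add a sensitivity analysis of outcome 10 that treats 30 s as right-censored, for example a censored-data mixed model at attempt level. It supplements the planned analysis and does not replace it.

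The cost is one flag per attempt and some extra analysis, with no change to how MBI is measured. The drawback for the sponsor is that the reported agreement may look less favourable.
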